### Setting

The study will be carried out in several urban areas of Navarra, in the North of Spain. Specifically, the six health centres in a community setting with the largest numbers of people diagnosed with PD will be chosen in order to maximise the recruitment of participants and improve the power of the study. At the end of the recruitment of participants, ANOVA and χ^2^ tests will be performed to explore the sociodemographic characteristics of the participants from the intervention group and the control group. In the case of finding a significant difference in a sociodemographic variable, the statistics analyses will adjust by propensity-score analysis or the most suitable statistical technique.

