### Procedure

There will be two groups in this study. Participants in group A will receive the ReNACE psychoeducational intervention while the participants in group B, belonging to the control group, will be given a general educational programme.

Allocation will be made according to the centre in which participants are attended. The experimental intervention was assigned to the centres in a random draw by tossing a coin (heads-control, tails-experimental) [27]. In this study individual randomisation, that is by patient or family carer, is not feasible because there is a high risk of contamination between intervention and control groups when participants interact with each other during their visits to their health centre. This is due to the patients from each health centre usually have the same family physician and nurse, and live in the same neighborhood. We decided to choose the six health centres with the highest numbers of people diagnosed with PD. With this proposed allocation strategy it is expected that contamination between the control and intervention groups will be minimal.

Furthermore, participants will be blinded to intervention assignment [28] as they will only be aware of the intervention they are receiving and they will not know if they belong to the intervention or control group. The healthcare professionals helping the participants in data collection will also be blinded to intervention assignment [28]. The healthcare professionals delivering the sessions to all the participants in the control and intervention groups will always be the same.

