### The intervention

The group A will participate in the ReNACE psychoeducational intervention for 9 weeks with one 90 min group session per week. The objective of the contents of this intervention is to foster the coping skills of the participants to facilitate and promote their psychosocial adjustment to PD. The sessions will take place in groups of 15–20 people at most so as to promote reflection and facilitate the interchange of opinions between participants about issues of interest from their day to day experience of coping with PD. Table 3 shows the organisation of the topics that will be dealt with in each weekly session.

**Table 3 Tab3:** Summary of the ReNACE psychoeducational intervention. Intervention group (A)

	Target audience	Topic	Provider
Session 1	Patients	Global introduction to the intervention	General practitioner
	Carers	Global introduction to the intervention	General practitioner
Session 2	Patients	Getting to know Parkinson’s disease	Neurologist
	Carers	Healthy life habits	Primary Care nurse
Session 3	Patients	Healthy life habits	Primary Care nurse
	Carers	Getting to know Parkinson’s disease	Neurologist
Session 4	Patients	Resources	Social worker
	Carers	Management of stress and complicated situations	Psychologist
Session 5	Patients	Adapting to and coping with Parkinson’s disease	General practitioner and Expert patient
	Carers	Resources	Social worker
Session 6	Patients	Positive self-esteem *&* Empathy and patience	Psychologist
	Carers	Look for information and live in the present *&* Normalise the situation and partake in activities	Psychologist
Session 7	Patients	Management of stress and complicated situations	Psychologist
	Carers	Positive self-esteem *&* Empathy and patience	Psychologist
Session 8	Patients	Look for information and live in the present *&* Normalise the situation and partake in activities	Psychologist
	Carers	Adapting to and coping with Parkinson’s disease	General practitioner and Expert patient
Session 9	Patients	Conclusions	General practitioner
	Carers	Conclusions	General practitioner

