### Data analysis

#### Quantitative data

Analysis of quantitative data will be performed on an intention to treat basis and for that SPSS version 23.0 will be used. A descriptive analysis of the sociodemographic data will be made. For the quantitative variables, means and standard deviations will be calculated. Mixed ANOVA within-pairs and between-pairs to compare patients with family carers at each measurement points, unpaired student t tests to determine any significant differences between the two groups at baseline (T0) and the measurements at T1 and T2 will be used. Also, a mixed factorial ANOVA with 1 between-subjects factor with 2 levels (intervention and control), and 1 within-subjects factor with 3 levels (baseline, time 1 post-intervention, time 2 post-intervention) will be used to compare differences between the two groups in the main variables over time. If any demographic variable result different will be use as a covariate in this analysis.

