### Limitations

The non-randomised and voluntary nature of the participation could limit the generalisation of results. However, statistical generalization is not sought in this study but a breakthrough in an area of interventional research that has been neglected for many years when it comes to PD and family carers and illness adjustment. In particular, patients at an advanced stage of PD may not take part in the intervention due to their disability and that young patients who have been diagnosed only recently may not enroll in the intervention due to the stigma of PD being thought of as a disease of the elderly. However, given that centres from different health areas of Navarra will participate, it is expected that the likelihood of this effect influencing the results will be diminished. Similarly, the reliability and sensitivity of the measurement scales that will be used in the study, together with the use of repeated measures, the presence of a control group and the baseline comparison between groups, are all important factors that will help to overcome the limitation mentioned above.

Another limitation could be the baseline differences between the centres selected in the quasi-experiment. However, it is expected that non-statistically significant differences will be found between participants given that the populations of the centres share a similar socio-economic and cultural context.

Furthermore, a limitation of this study is to successfully encourage people with PD and their family carers, who generally do not participate in activities on a regular basis, to attend the intervention each week. It is necessary to bear in mind that given the age and physical condition of the target population the number of subjects lost to the study could be greater than usual in longitudinal studies. However, to minimise this effect, at the end of each session participants will receive a small introduction to the topic of the following week which will help to increase enthusiasm and promote regular attendance.

It is also necessary to point out that in this study it is not possible for the professionals giving the sessions to be blinded, given that there are two different types of intervention. However, researchers involved in the data collection and participants for group A and B will be blinded to the intervention. Also the content and methodology of each session will be established previously in a manual that the professionals will use.

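### Treatment is allocated by health centre, but the planned between-arm tests have no centre or session-group term, so they ignore clustering in a contrast that rests on six centres

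*Protocol article*

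**What the plan says.** **Allocation.** Under Procedure: "Allocation will be made according to the centre in which participants are attended", and "The experimental intervention was assigned to the centres in a random draw by tossing a coin". Setting describes the sites as "the six health centres in a community setting with the largest numbers of people diagnosed with PD". The article does not say how many centres fell in each arm.

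**Likeness within centres.** Procedure rejects individual randomisation because of contamination, noting that "the patients from each health centre usually have the same family physician and nurse, and live in the same neighborhood".

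**Delivery.** The intervention section states: "The sessions will take place in groups of 15–20 people at most". The control programme has the same group-size limit. Procedure adds that the same professionals deliver the sessions in both arms.

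**Analysis.** Data analysis (Quantitative data) plans unpaired t tests between arms at T0, T1 and T2, and "a mixed factorial ANOVA with 1 between-subjects factor with 2 levels (intervention and control), and 1 within-subjects factor with 3 levels". It also plans a within-pairs and between-pairs ANOVA for patients against carers. Demographic variables that differ become covariates. Setting adds propensity-score adjustment, or another suitable technique, if a sociodemographic variable differs significantly. Centre and session group appear in none of these.

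**Primary outcome.** Outcome measures defines it as improvement in quality of life with the ReNACE programme compared with the change under the general programme.

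**The concern.** People treated at the same centre, and in the same session group, may have correlated outcomes. When treatment is assigned by centre, that correlation adds directly to the variance of the difference between arms. A t test or ANOVA with individual-level error leaves it out. With 39 evaluable patients per arm, the t test uses 76 error df, whereas six centres in two arms supply 4.

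If the correlation is positive, standard errors are too small and p-values too low. The comparison affected is the quality-of-life contrast that the authors hope will support adoption in Primary Care. A centre-level difference, or a centre-specific change in the case of the group-by-time test, could then be read as a treatment effect.

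**Working it through.** **Inputs from the article.** Six centres; Table 2: patients SD 15.44, difference 10, power 80%, losses 25%, 52 per group; carers SD 25.04, difference 15, power 80%, losses 20%, 53 per group.

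**Assumptions (not in the article).** Two-sided alpha 0.05; three centres per arm of equal size; ICC from 0.01 to 0.10; within-person correlation r = 0.6 for the repeated-measures test.

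**1. Reproduce the stated sample size.** n per arm = 2(1.960 + 0.842)² SD²/difference².
- Patients: 2 × 7.849 × 238.4/100 = 37.4, so 38 (39 with the t distribution). 39/0.75 = 52, as stated.
- Carers: 2 × 7.849 × 627.0/225 = 43.7, so 44. 44 × 1.2 = 52.8, so 53 as stated; dividing by 0.80 instead gives 55.

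Both figures follow from an individually allocated two-sample comparison with no design effect.

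**2. T1 and T2 t tests.** Evaluable patients: 52 × 0.75 = 39 per arm, or m = 13 per centre. Carers: 53 × 0.80 = 42, or m = 14. Design effect DE = 1 + (m − 1) × ICC; true type I error ≈ 2[1 − Φ(1.96/√DE)].

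| ICC | DE, patients | True SE / naive SE | Type I, patients | Type I, carers |
|---|---|---|---|---|
| 0.01 | 1.12 | 1.06 | 6.4% | 6.5% |
| 0.02 | 1.24 | 1.11 | 7.8% | 8.1% |
| 0.05 | 1.60 | 1.26 | 12.1% | 12.7% |
| 0.10 | 2.20 | 1.48 | 18.6% | 19.6% |

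Simulation of the patient t test (20,000 runs) gave 6.2%, 8.1%, 12.1% and 18.9%.

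**3. Group-by-time F test.** Simulated with 2 × 39 patients, three centres per arm, three time points, r = 0.6, df 2 and 2 × (78 − 2) = 152.
- Constant centre effect (ICC 0.05 or 0.10): about 5%, because it cancels from within-person change.
- Centre-by-time variance 1%, 2% or 5% of the total: about 10%, 15% and 30%. Repeat runs, including one with r near 0.5, gave 9–10%, 14–16% and 28–31%.

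**4. Test on centre means.** A t test on six centre means (4 df, critical value 2.78) held about 5% in every scenario, for post-scores and for change scores. Its power for the 10-point patient difference on post-scores uses a noncentral t with noncentrality (10/15.44)/√(2·DE/39):

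| ICC | Noncentrality | Power |
|---|---|---|
| 0 | 2.86 | 58% |
| 0.01 | 2.70 | 54% |
| 0.02 | 2.57 | 50% |
| 0.05 | 2.26 | 41% |
| 0.10 | 1.93 | 32% |

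The stated 80% holds only for individually allocated patients (39 per arm gives 80.6% by t test).

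**The case against.** **The tests do not ignore all dependence.** The factorial ANOVA models repeated measures, and another ANOVA recognises patient–carer pairs. A reader might infer that every planned test treats participants as independent. That goes too far: what is missing is clustering by centre and session group.

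**The largest t-test figures belong to the less relevant test.** The primary outcome compares change, which the group-by-time test addresses. Stable differences between centres cancel there. The shared physician, nurse and neighbourhood point most directly to stable differences, and the article offers them as a contamination argument, not as a statement about correlated outcomes. Having the same professionals deliver all sessions removes one source of centre-specific change. This stands, and it makes the size of any inflation in that test unknown. Group dynamics remain a plausible source of centre-specific change.

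**The numbers rest on assumptions.** The article gives no alpha, ICC or split, and at ICC 0.01 the t-test excess is small. This also stands. A reader might infer that false positives certainly exceed 5%. The article supports only a conditional statement: they do in the t tests for any positive ICC, and in the group-by-time test only if centre effects change over time.

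**Other clauses might cover it.** The open-ended adjustment in Setting is triggered only by sociodemographic imbalance, and neither a covariate nor a propensity score corrects a standard error for clustering. The analysis model is written out with its factors, so this is not a detail left to an unseen analysis plan. The statement in Limitations that "The non-randomised and voluntary nature of the participation could limit the generalisation of results" concerns generalisability. It neither shows the clustering error nor excuses it. The article also does not say that session groups are closed, and nothing here depends on that.

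**Conclusion.** The point holds in this form: the between-arm tests, as specified, do not match the unit of allocation. They take their error from individuals although the contrast rests on six centres. The direction for the T1 and T2 t tests is certain for any positive ICC; the size depends on an ICC that the article does not give. For the group-by-time test the planned analysis is close to nominal if centre effects are constant, and can be badly anti-conservative under even modest centre-specific change. Nothing in the article shows which applies.

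The tabulated sizes assume equal centres split three and three. An unequal split would lower the power of a centre-level test further. This needs correcting before the quantitative analysis, because it affects the primary comparison.

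**What to change.** 1. Make the primary between-arm analysis a comparison of baseline-adjusted or change-score centre means on about 4 df. Alternatively, fit a linear mixed model with random centre and centre-by-time effects and Kenward–Roger or Satterthwaite df, where estimable. With six centres the variance components may be estimated at zero or be unstable, and session group may be hard to separate from centre, so the centre-level analysis is the safer choice.
2. Report the individual-level t tests and factorial ANOVA as exploratory.
3. Describe the design as cluster-allocated and state the number of centres per arm. Reconcile the random draw in Procedure with the non-randomised wording in Limitations.
4. Restate the power in Sample size for the actual design, giving the assumed ICC range.

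**Cost.** No new data are needed, since allocation already identifies each participant's centre. But this is more than a change of wording: intervals widen, and the 80% power claim cannot be kept. The post-score powers above are the guide; baseline adjustment may recover some power, by an amount that the article gives no figures to estimate. Recruitment began in 2015 in a fixed set of six centres, so the loss should be disclosed. No added enrolment is proposed.

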#### Qualitative data

An in-depth analysis will be made of the transcriptions of the focal groups using content analysis [35]. The Nvivo® programme will be used to facilitate the handling and storage of the data. Analysis of the data will begin after the first focus group has been organised so that the results will help to enrich successive data collection. Analysis of the data will be performed individually by two researchers who will then meet to compare codes, categories and themes identified and to agree on the final results.

### Ethical considerations

Ethical approval for this study was obtained from the Ethics Committee of the University of Navarre in May 2014. After this, approvals from the participating centres were gained. Participants will sign an informed consent form that state their decision to take part in the study is voluntary, do not affect to their healthcare and that they can leave the study at any time. All personal information will be kept confidential. This information will be explained by a researcher to the participants in order to solve any doubt.

### Validity and reliability

The contents of the ReNACE psychoeducational intervention have been designed on the basis of previous research [11, 14, 21, 36, 37] carried out by the ReNACE programme team. This research highlighted the relevance that coping and adjustment have for living with PD in a positive way, both in patients and family carers. It further underlined the influence that exists between coping and adjustment and in turn between adjustment to PD and quality of life in this population [11, 18]. Furthermore, the present study will be conducted according to the philosophy of the Chronic Care Model [38]. Therefore, the strengthening of trust and motivation in participants for taking care of their health and coping skills will be an essential feature of the psychoeducational intervention. This study follows the recommendations of SPIRIT in the protocol and of the World Health Organization in the trial registration data. So as the qualitative methods of the study, researcher triangulation to validate the analysis of the data will take place as described [39].

## Discussion

This article describes the protocol of a quasi-experimental study with a control group and mixed methods designed to determine the effectiveness of a multidisciplinary psychoeducational intervention aimed at improving the quality of life of people with PD and their carers.

In the literature some non-pharmacological interventions have been identified [13, 19, 20, 24, 40–42] which sought to enable people with PD to deal with the different consequences of living with their illness. Although, in only two interventions [19, 20] were the development of coping skills and improvement in the psychosocial adjustment to PD promoted, no measurement was made of the changes occurring in these aspects. In accordance with the experience provided by these previous interventions [13, 19, 20, 24, 40–42], it is foreseen that the present quasi-experiment will be able to be carried out adequately in the target population.

Furthermore, as in the majority of previous interventions [20, 24, 40, 42], it is expected that with the ReNACE psychoeducational intervention statistically significant results will be obtained in the short-term, immediately after the end of the intervention. As for the evaluation of long-term results, in most of the studies conducted no statistically significant long-term results were obtained [20, 42] or they were not evaluated [19, 24, 41]. This shows the complexity involved in enabling people with PD to continue coping with the new situations that they will encounter when living with this neurodegenerative disease once the intervention period has finished but the progression of the disease and its consequences continues. However, the results of two randomised controlled trials into PD [13, 40] and a systematic review in LTCs [43] suggest that interventions focusing on improving lifestyles, redefinition of biography, social networks, emotional wellbeing and activities of daily life, such as the ReNACE intervention (see Table 3), represent tools with a great potential to help people with LTCs to know in the long-term how to deal with the difficulties caused by living with the disease. Specifically, considering the dynamic nature of the process of coping and adjustment to PD, this is where Primary Care professionals could play a vital role because if we demonstrate that these types of interventions are effective and feasible through projects, its continuation and reinforcement from a clinical perspective in the community will be the next step for the long term sustainability of the improvements and transformation of care pathways.

Furthermore, it is worth noting the small number of studies that have taken into account the need to train the family carers of patients with PD. However, there is an increasing number of authors [9–11, 36] who underline the importance of engaging family carers in a training process that allows them to better cope with the experience of the LTC. For this reason, in the quasi-experiment that we propose, the family carers will receive sessions with information suitable for their needs and this will clearly contribute to one of the big gaps in the literature when it comes to educating and caring from PD patients and family carers as a family unit.

The present quasi-experimental study aims to demonstrate the benefits that patients with PD and their family carers can obtain if they receive psychosocial care oriented towards health promotion. However, the ultimate goal of this research is to achieve the full incorporation of the proposed psychoeducational intervention into the daily practice of the different social and healthcare professionals that interact with patients with PD and their family members.

Consequently, this study although at a small scale constitutes an important research and conceptual leap in the available literature, which lacks evidence of interventions for people with PD and family carers as a whole and seeks an approximation between the research and the clinical reality in Primary Care. Furthermore, the psychosocial nature of the proposed intervention approaches a neglected area in research and practice, which will clearly contribute to reduce the burden of PD for patients and family carers and the existing knowledge [44, 45].

It is expected that the results of the study will contribute to the creation of similar psychoeducational interventions for people with other LTCs and their family carers. In the long-term it is hoped that this type of intervention will help to consolidate a sustainable care network, which will fully cover the needs of people with LTCs and their families thus favoring their emotional wellbeing, social life, biography and a healthy lifestyle.

### Limitations

The non-randomised and voluntary nature of the participation could limit the generalisation of results. However, statistical generalization is not sought in this study but a breakthrough in an area of interventional research that has been neglected for many years when it comes to PD and family carers and illness adjustment. In particular, patients at an advanced stage of PD may not take part in the intervention due to their disability and that young patients who have been diagnosed only recently may not enroll in the intervention due to the stigma of PD being thought of as a disease of the elderly. However, given that centres from different health areas of Navarra will participate, it is expected that the likelihood of this effect influencing the results will be diminished. Similarly, the reliability and sensitivity of the measurement scales that will be used in the study, together with the use of repeated measures, the presence of a control group and the baseline comparison between groups, are all important factors that will help to overcome the limitation mentioned above.

Another limitation could be the baseline differences between the centres selected in the quasi-experiment. However, it is expected that non-statistically significant differences will be found between participants given that the populations of the centres share a similar socio-economic and cultural context.

Furthermore, a limitation of this study is to successfully encourage people with PD and their family carers, who generally do not participate in activities on a regular basis, to attend the intervention each week. It is necessary to bear in mind that given the age and physical condition of the target population the number of subjects lost to the study could be greater than usual in longitudinal studies. However, to minimise this effect, at the end of each session participants will receive a small introduction to the topic of the following week which will help to increase enthusiasm and promote regular attendance.

It is also necessary to point out that in this study it is not possible for the professionals giving the sessions to be blinded, given that there are two different types of intervention. However, researchers involved in the data collection and participants for group A and B will be blinded to the intervention. Also the content and methodology of each session will be established previously in a manual that the professionals will use.

A final potential limitation of this study is that two types of data collection will be used. At measurement points T0 (baseline) and T1 (post-intervention) all participants will be given an appointment at their health centre to fill in the questionnaire the same day. In contrast, at measurement point T2 (6 months post-intervention) participants will receive the questionnaire by post and will fill it in in their homes. Nevertheless, given that the participants will have completed the questionnaire on two previous occasions no difficulties are expected for completing the questionnaire at measurement point T2 and doubts will be solved when needed. Moreover, to avoid high numbers of participants not returning or forgetting returning the questionnaire at T2, health professionals from the health centres will be involved in the follow up.

